**Other Variables**					
**VHA Patient Satisfaction Survey**			x		x
**Computer Email Web Literacy (CEW)**	x				

### Recruitment and Screening Procedures

The study procedures are approved by the Institutional Review Board at the Hines VA Medical Center. Participants who pass initial eligibility screening, will then undergo a written informed consent process prior to beginning the study protocol. To be eligible, veterans must be enrolled in the *MOVE! *group at the Hines Hospital VAMC with BMI ≥ 25 and ≤ 40 and weigh < 400 pounds, experience chronic pain ( ≥ 4 on the NRS-I scale for ≥ 6 months prior to enrollment) and are able to participate in a moderate intensity exercise program will be recruited. The enrollment policy is consistent with the 2005 VA/DoD Practice Guideline that recommends obesity treatment for all Veterans with BMI ≥ 25 and consideration of supplemental pharmacotherapy and surgical treatments for severely obese patients with BMI ≥ 40 [51]. Further eligibility criteria is listed in Table 2.

**Table 2 T2:** Eligibility Criteria

Eligibility Criteria
• Willing to participate in a 12-month study
• Independently Mobile (no cane, walker, wheelchair needed)
• Can participate in regular exercise
• No psychiatric hospitalizations within the past year
• No cognitive or sensorimotor impairment
• Cannot participate in a structured diet program outside of study
• Cannot be at high risk for adverse CVD events while exercising
• Considering making changes to lose weight in the next 6 months^1^
• Absence of any substance abuse, mood, or binge eating disorder that would interfere with adherence^2^
• Must experience chronic pain (≥ 4 on the NRS-I scale for ≥ 6 months prior to enrollment)

^1^As measured by the Exercise and Weight Stages of Change Form

^2^As measured by the PRIME-MD

### Training

All eligible participants will receive and be trained to properly use the PDA to report dietary intake (that is automatically time and date stamped), moderate intensity physical activity minutes, and weight from a digital scale to the coach. An exclusionary competency check is administered to ensure that the participant can accurately enter a sample meal, minutes of physical activity, and their weight into the PDA. Once demonstrated, the participants will begin recording baseline data and will be scheduled for a randomization session in 7-14 days.

### Baseline Period

Baseline is a two week period in which the participant records food intake, weight, and activity into the PDA and uploads data to the study server each night. During the baseline period, participants will be required to meet the following eligibility criteria: a) record ≥ 2 meals per day and have ≥ 2 items per meal recorded, and b) record their daily weight in the morning. Coaches will provide corrective feedback when implausible reports suggest inaccurate or untimely recording (i.e: only 500 calories consumed the entire day). During the baseline phase, the intake and expenditure thermometers will not be visible to the participants. Randomization will occur if all eligibility criteria are met.

### Randomization

Prior to randomization and to discourage heightened attrition in the control group, a brief motivational interviewing intervention will be performed to make salient the pros and cons of being randomized to either condition. Participants will be re-assessed about their readiness to make lifestyle changes by administering the Exercise and Weight Stages of Change Short Forms [42] to identify and exclude pre-contemplators.

Participants will be randomly assigned to one of two groups: a) Standard Care or b) Standard Care +PDA (PDA+). Group randomization will be computer-generated via the method of randomly permuted blocks. The use of permuted blocks preserves balance in the randomization over the course of the study, to maintain equal sample sizes in the two experimental conditions. Randomization will be stratified by age (≤ 65 vs. > 65), BMI (< 35 vs. ≥ 35), and gender, to maintain equal numbers of women and men in each treatment condition.

Once randomized, those in the standard care group will no longer record their intake, weight, or activity using the PDA. The group will return all study equipment and attend *MOVE! *groups and follow-up lab sessions as scheduled.

Since the proposed design is additive (i.e., it tests the effects of adding technology and coaching to standard care), it is important to establish that the standard care received by participants is equivalent across conditions (e.g., entails comparable intervention components and level of interventionist expertise). To prevent contamination, *MOVE! *group leaders will be different individuals than those who train and coach participants randomized to the PDA conditions.

## Weight Loss Phase (months 1-6)

### Calorie and Weight Loss Goals

Patients randomized to the treatment group will continue to upload their dietary data daily, as well as their mood, pain level, and accelerometer data (Figure 2). Successful completion of 7 days of PDA uploading meets the mastery criterion for recording and uploading, and will trigger activation of the PDA's treatment protocol (Figure 3). Rather than progressing through eating goals in a lockstep manner at fixed time intervals, progress will be mastery-based (triggered by accomplishment of each prior goal), which will help to minimize frustration and failure and reinforce intrinsic motivation.

**Figure 2 F2:**
[figure not shown]
**Screen shot of the goal thermometers**. The goal thermometers reflect the calories and moderate activity of a hypothetical participant.

**Figure 3 F3:**
[figure not shown]
**Protocol Timeline**. Participant progression through the study protocol

Every two weeks for the next 6 months, coaches will review participants' data to evaluate if they have met their weight loss, calorie, and behavioral goals. If, after meeting their caloric goals, participants do not lose weight for two consecutive weeks, they will be instructed to reduce calories in 100 kcal increments until they reach a calorie intake level that yields a weight loss rate of .5-1% of their current weight per week. No patient will be given an intake goal below 1200 kcal per day. Conversely, if the rate of weight loss is too rapid (operationalized as weight loss of ≥ 3 pounds/week for 4 consecutive weeks), calorie intake goal will be increased in 100 kcal increments until attainment of the goal of .5-1% of current weight is lost per week for two weeks is achieved.

### Physical Activity Goals

Once participants have been provided with calorie intake goals for four weeks, a physical activity goal will be added. Coaches will assist participants in determining the types of activities that are ideal, which are based on interest, skill, and conditioning level. Physical activity goals are calculated and assigned using algorithms that set the treatment goals in a stepwise fashion, such that forward progression is mastery-based (i.e., patient proceeds to next goal only after first goal has been met).

## Maintenance Phase (months 7-12)

During the maintenance phase, the focus is to maintain goals set during the weight loss phase of the study. Participants are required to upload two weeks per month in months 7-9, and one week per month in months 10-12. The coach will monitor data uploads and remind participants to record and upload data if it is not completed during the pre-designated time points.

## Data Analysis

### Sample Size & Power Estimate

Sample size calculations were determined using a large VA sample provided by National Center for Health Promotion and Disease Prevention (NCP) to estimate weight loss achieved by *MOVE! *participants during a 6-month period. VA NCP data show that *MOVE! *patients who attended at least one group visit showed a weight loss of 6.36 lbs (s.d. = 11.68; N = 166) over 6 months [52]. Additionally, these same subjects had a correlation of .977 between their baseline and 6-month follow-up weight measurements. Accordingly, we expect the Standard Care group's weight loss to be 6 lb (s.d. = 12) over 6 months, and we conservatively assume this same weight loss level to be maintained at 12 months. A clinically meaningful increment in weight loss would occur if adding the PDA decision support tool produced a 12 lb. weight loss. Thus, we posit a 6 lb difference between our control and intervention groups.

To calculate power in terms of a comparison of weight measurements over time, we used methods described in Hedeker et al [53]. For this, we assume that there will be 75 participants per group at baseline, and an attrition rate of 4% at each measurement wave (i.e., an overall retention rate of 85% at 12-months). We also conservatively assume, based on the aforementioned VA study, that the correlation of the repeated weight measurements equals .95. Given these assumptions, power is in excess of .80 for a two-tailed .05 hypothesis test for the standard care versus PDA+ group contrast comparing baseline weight versus weight at all follow-up measurements (i.e., 3-, 6-, 9-, and 12-month follow-ups) under the following scenario: a 0 lb group difference at baseline and a 6 lb group difference at all subsequent timepoints (i.e., an effect size of 6/50 = .12 at these four follow-up timepoints).

For comparing weight at specific timepoints, we considered power in terms of weight change at the final timepoint, since it is at that timepoint that the sample is smallest. At 12 months, we expect there to be 75 × .85 = 64 subjects per group. If we again assume a clinically meaningful difference of 6 pounds, and given the standard deviation of 12 for weight change from the VA study, we are interested in an effect size of .5 SD units. For this, power is in excess of .80 for a two-tailed .05 hypothesis test for this comparison at the final timepoint.

### Analysis

Outcomes will be analyzed longitudinally on an intent-to-treat basis. Our general analytic approach will be to use longitudinal mixed-effects regression models (MRMs) implemented via SAS PROC MIXED. A priori contrasts will be estimated for the standard care versus PDA+ comparison. We will also include all stratification variables (age, BMI, gender) in all analyses.

Following the guidelines of Fitzmaurice and colleagues (2004) we will model weight (in lbs) at all timepoints (baseline, 3-, 6-, 9, and 12-months) including both linear and quadratic effects of time (to allow for curvilinearity in weight across time), and group by time interactions [54]. As these authors recommend, we will include baseline weight as part of the dependent variable vector, and further assume that the group means are equal at baseline. This approach yields a valid estimate of treatment group comparisons that is generally more powerful than other alternatives. Our primary tests will be for the presence of the group by time interaction terms, which will indicate the degree to which group differences in weight are present after baseline, and the degree to which any group differences are maintained over time

Though MRMs permit missing data across time, they do assume that the missing data are missing at random (MAR). MAR allows the missingness to be related to covariates (i.e., time, group, initial BMI) and also observed values of the dependent variable across time (i.e., a subject's observed weight measurements). Since many experts advise that MAR analysis is reasonable for most longitudinal clinical trials, we will use our MRM analysis as the primary approach [54,55]. However, we will also conduct sensitivity analyses to examine how robust our results are to missing data aspects using models that go beyond MAR. Specifically, we will additionally estimate pattern-mixture models [56] and shared parameter or selection models [57] to give us a sense if our conclusions vary at all by assumptions regarding the missing data.

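### After randomization only PDA+ participants have coaches, who are almost certainly shared, yet the power calculation allows nothing for coach clustering and the model as described names no coach term

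*Protocol article*

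**What the plan says.** **Coaching.** The Study Aims make personalized coaching part of the tested package. Under Data Collection, PDA+ participants send their data to their own coach each week. Under Calorie and Weight Loss Goals, coaches (plural) check the data every two weeks for six months "to evaluate if they have met their weight loss, calorie, and behavioral goals". Under Maintenance Phase, the coach follows up missing uploads in months 7 to 12. The Randomization section keeps the MOVE! group leaders separate from "those who train and coach participants randomized to the PDA conditions". Once randomized, Standard Care participants return their equipment, and no coach is described for them from then on.

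**Model.** The Study Design section names two factors, treatment and time. The Analysis section names "longitudinal mixed-effects regression models (MRMs) implemented via SAS PROC MIXED", with linear and quadratic time, group by time, and age, BMI and gender. It plans sensitivity analyses for missing data only.

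**Power.** The Sample Size section states "we assume that there will be 75 participants per group at baseline", "we posit a 6 lb difference between our control and intervention groups" and, for the 12-month comparison, "given the standard deviation of 12 for weight change from the VA study". With 64 per group retained it concludes that "power is in excess of .80 for a two-tailed .05 hypothesis test for this comparison at the final timepoint". Its inputs are numbers of participants, attrition, within-person correlation and standard deviations.

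**The concern.** Participants who share a coach share that coach's skill, persistence and judgement, so their weight changes may be correlated. Here that can happen after randomization in one arm only. A model with no coach level sets the coach variance to zero, which is the least conservative value available.

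If the true value is positive, there are two consequences. An analysis that ignores it uses too small a standard error and rejects a true null hypothesis more often than 5% of the time. An analysis that respects it has less power than the plan states. The second matters because the 12-month figure has almost no margin.

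**Working it through.** **Inputs from the Sample Size section:** 64 per group at 12 months (75 × .85), difference 6 lb, SD of change 12 lb, two-sided alpha .05.

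**Inputs assumed, because the article gives none:** K = 2 to 6 coaches with equal caseloads, ICC of 12-month weight change .01 to .05, and total SD held at 12 lb.

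**Step 1. Reproduce the plan's figure under independence.** SE = 12 × √(2/64) = 2.121 lb, and 6/2.121 = 2.828. Power = Φ(2.828 − 1.960) = .807. The noncentral t gives .801. The normal formula requires 63 per group, and 64 are expected. The stated figure therefore holds, with one participant per group to spare.

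**Step 2. Add coach clustering in PDA+ only.** With m = 64/K participants per coach:
- Design effect in PDA+: DE = 1 + (m − 1) × ICC
- Ratio of true to naive standard error: R = √((1 + DE)/2)
- Actual type I error if clustering is ignored: 2 × (1 − Φ(1.96/R))
- Power with the correct standard error: Φ(2.828/R − 1.96)

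| Coaches | ICC | DE | R | Type I error | Power |
|---|---|---|---|---|---|
| 6 | .01 | 1.10 | 1.02 | .056 | .789 |
| 4 | .02 | 1.30 | 1.07 | .068 | .751 |
| 3 | .02 | 1.41 | 1.10 | .074 | .732 |
| 6 | .05 | 1.48 | 1.11 | .079 | .718 |
| 3 | .05 | 2.02 | 1.23 | .111 | .634 |
| 2 | .05 | 2.55 | 1.33 | .141 | .565 |

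The last two columns describe different analyses: the type I error is for one that ignores coaches, the power for one that does not.

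**Step 3. Find the break-even.** Power is exactly .80 when (6/(1.960 + .8416))² × 64/144 = 1 + DE, which gives DE = 1.0385. Then ICC = .0385/(64/K − 1):
- 3 coaches: .0385/20.33 = .0019
- 6 coaches: .0385/9.67 = .0040

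**Step 4. Allow for few coaches.** The normal approximation flatters the corrected analysis. With Satterthwaite degrees of freedom, 3 to 6 coaches and ICC .01 to .05 give power from .74 down to .44.

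The arithmetic is confined to the 12-month comparison. The power statement for the contrast over all follow-ups likewise has no coach allowance.

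**The case against.** **The model half argues from silence.** This is a condensed article. It lists fixed effects and spells out no random-effects structure, so a reader might infer that the trial has committed itself to a model of independent participants. The text does not say that, and the full plan may contain more. This objection stands: the model half rests only on the terms named. It does not reach the power half, because the article states the inputs and conclusion there and they reproduce only under independence.

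**The size is unknown.** A reader might infer that the confidence intervals are too narrow as a matter of fact. The documents do not support that, because they give no coach number, caseload or ICC. There are also reasons to expect a small effect: calorie goals follow set triggers, activity goals come from algorithms, the PDA gives automated feedback, and telephone support ends at six months while the power figure is for month 12. This stands too, and the high end of the range needs 2 coaches and ICC .05 together.

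**It is too strong to say that any coach effect breaks the .80.** By the normal formula, 6 coaches with ICC .003 still give .802. The plan also rounds the source SD of 11.68 up to 12. At 11.68 the t-based power is .822, and the break-even is DE = 4.587 × 64/136.4 − 1 = 1.152, or ICC .007 (3 coaches) to .016 (6 coaches). The mixed model also uses earlier data from dropouts. These give some slack, but the power statement claims none of it.

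**Controls do meet coaches.** Coaches give corrective feedback to all participants in the baseline period. A reader might infer that controls never have a coach; that is true only after randomization. The earlier contact precedes allocation and does not remove the one-arm nesting that follows.

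**A random coach effect is a choice.** Treating this site's coaches as part of the package is defensible, and it limits the conclusion to those coaches. That is a good reason to leave the primary model alone, but not a reason against a sensitivity analysis.

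**Conclusion.** The point holds as a conditional one and is a modest improvement, not a serious flaw. PDA+ is very probably nested in a few coaches after randomization and Standard Care is not. Sharing of coaches is inferred from 75 participants and the plural, not stated. The stated 12-month power is correct under independence, at .801 to .807, and falls below .80 at an ICC of about .002 to .004 for 3 to 6 coaches with the plan's own SD.

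Over the assumed range of 2 to 6 coaches and ICC .01 to .05, the understatement runs from negligible (standard error 2% larger, type I error .056, power .79) to substantial (33%, .141, .57). If the ICC is zero, nothing changes. The documents cannot say where in that range the trial lies.

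**What to change.** 1. Record each PDA+ participant's coach, and any change of coach, while the trial runs. The check may be impossible later without this.
2. Keep the primary model. Prespecify a sensitivity analysis that adds a coach random effect on follow-up weight in PDA+ only (zero in Standard Care), with small-sample degrees of freedom.
3. If the coach variance cannot be estimated, report the treatment confidence interval with the PDA+ variance inflated over a stated ICC range, for example .01 to .05.
4. In the power section, state that the claim of power above .80 assumes no coach clustering. Give the actual number of coaches and the power over the same ICC range.

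The cost is one recorded variable, one extra model and a line or two of text. The downside is wider intervals in the sensitivity analysis and an imprecise coach variance if there are few coaches.

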## Methods

### Study Design

The research design is a 2 × 5 factorial involving one between subject's factor (treatment condition) with 2 levels (Standard Care vs. Standard Care+ PDA (PDA+) and one within subject's factor (time) with 5 levels (randomization, 3-, 6-, 9-, and 12-month follow-up). Participants will be followed through three trial phases (Figure 1).

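### The stated power belongs to a baseline-versus-follow-up contrast, but the primary tests are linear and quadratic group-by-time terms, which cannot reproduce the planned effect shape

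*Protocol article*

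**What the plan says.** The Sample Size & Power Estimate section states that "power is in excess of .80 for a two-tailed .05 hypothesis test for the standard care versus PDA+ group contrast", and defines that contrast as "comparing baseline weight versus weight at all follow-up measurements". The scenario is "a 0 lb group difference at baseline and a 6 lb group difference at all subsequent timepoints", described as "an effect size of 6/50 = .12 at these four follow-up timepoints", and it is assumed that "the correlation of the repeated weight measurements equals .95". A second calculation covers weight change at 12 months (64 per group, 6 lb, change SD 12).

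The Analysis section fits weight at all five occasions, "including both linear and quadratic effects of time (to allow for curvilinearity in weight across time"), with group-by-time interactions, baseline weight in the response vector and equal group means at baseline. It then says "Our primary tests will be for the presence of the group by time interaction terms", and that these terms will show both whether groups differ after baseline and how far any difference is maintained. A priori group contrasts are mentioned, but they are neither defined nor called primary.

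**The concern.** The test named as primary is not the test that was powered, and no power is given for the named one. The powered contrast spends one degree of freedom on the average follow-up difference. The interaction terms spend two, on the initial slope and the curvature of a difference curve.

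The curve is also forced through zero at baseline, so it cannot take the step shape used for planning. Two things are at stake. The power claim may not carry over to the primary analysis. And 12-month maintenance, one of the primary aims, would be read from a curve that can bend downward even when the true difference is constant.

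**Working it through.** **Inputs** (Sample Size & Power Estimate): 75 per group; 4% loss per wave, giving 75, 72, 69.1, 66.4 and 63.7 per group; SD 50 (the denominator of 6/50); correlation .95, read as one common value (compound symmetry); difference 0, 6, 6, 6, 6 lb; two-sided .05.

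**Step 1: reproduce the stated power.** Take c = (−1, ¼, ¼, ¼, ¼) and Var = 2 Σ cᵢcⱼVᵢⱼ/√(nᵢnⱼ). Under compound symmetry this splits into two parts:

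- 2500 × .05 × Σcᵢ²/nᵢ = 125 × .01703 = 2.129
- 2500 × .95 × (Σcᵢ/√nᵢ)² = 2375 × (.00608)² = 0.088

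Var = 2 × (2.129 + 0.088) = 4.43, so SE = 2.105, z = 6/2.105 = 2.85 and power = .81. Generalized least squares (GLS) with dropout patterns and categorical time gives SE 2.108 and power .81. With equal baseline means it gives SE 2.068 and power .83. The stated figure is right for the contrast it describes.

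**Step 2: the named primary test on the same inputs.** Fixed effects are 1, t, t², group×t and group×t² (t in years), with no group main effect. The noncentrality of the joint Wald test is 7.27. Against a 2-df chi-square this gives power .67 (.65 without the equal-baseline constraint). Tested singly, the linear term has .62 and the quadratic term .41.

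**Step 3: the shape.** The modelled difference is d(t) = b₁t + b₂t². Requiring d = 6 at 3 and 6 months gives b₁ = 36 and b₂ = −48. Then d(.75) = 27 − 27 = 0 and d(1) = 36 − 48 = −12. No such curve equals 6 at all four visits. The GLS fit to the planned difference is b₁ = 18.92, b₂ = −14.09:

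| Month | True (lb) | Expected fit (lb) |
|---|---|---|
| 3 | 6 | 3.85 |
| 6 | 6 | 5.94 |
| 9 | 6 | 6.26 |
| 12 | 6 | 4.82 |

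The 12-month shortfall is (6 − 4.82)/6, about 20%.

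**Step 4: how far this depends on the inputs.** SD 50 with correlation .95 implies a change SD of 50√(2 × .05) = 15.8 lb, more than the 12 lb of the second power calculation.

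| Covariance, true difference | Powered contrast | Joint 2-df test | 12-month fit (lb) |
|---|---|---|---|
| Compound symmetry, SD 50, .95; step | .81–.83 | .67 | 4.8 |
| Compound symmetry, change SD 12, .95; step | .96–.97 | .90 | 4.8 |
| Compound symmetry, SD 50, .977; step | .98–.99 | .95 | 4.8 |
| AR(1), SD 50, .95; step | .39–.42 | .41 | 6.0 |
| Compound symmetry, SD 50, .95; 0,3,6,6,6 | .72 | .72 | 6.0 |

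Under AR(1) the misfit moves to 3 and 9 months (4.3 and 7.3 lb). The last row is an illustrative gradual onset, not a figure from the protocol; its contrast power is the equal-baseline value.

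**Step 5: candidate replacements** (categorical time, equal baselines, first-row inputs): averaged contrast .83; 6-month difference 6/2.643, z = 2.27, power .62; 12-month difference .60; 4-df group-by-visit test .63.

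**The case against.** The strongest reply is that the step is a simplification for the power calculation, not a forecast. Goals are mastery-based, and the activity goal comes only after four weeks of calorie goals, so the difference probably builds up. With 0,3,6,6,6 the quadratic fits 12 months at 6.0 lb, and the 2-df test has the same power as the contrast. The protocol also calls .95 conservative: on its observed correlation of .977, or its change SD of 12, the 2-df test is well above .80. These points stand. They limit the size of the problem, but they do not make the named test the powered one.

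A reader might infer more than the document supports:

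- *The trial is underpowered at .67.* That figure holds only for SD 50, correlation .95 and compound symmetry.
- *The 12-month effect will be understated by 20%.* That needs the full 6 lb by month 3. It persists when a random slope is added, but not under AR(1) or a gradual onset.
- *Type I error is inflated by testing two terms.* The text does not say that the terms are tested separately and unadjusted.
- *The design section contradicts the polynomial.* "one within subject's factor (time) with 5 levels" describes five measurement occasions, and a polynomial over five occasions is compatible with that.

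Details of the unnamed a priori contrasts may properly sit in an analysis plan that is not shown. The mismatch does not depend on them, because the article itself states both the powered contrast and the primary test.

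**Conclusion.** The point holds and should be fixed. The claim of power over .80 is correct for the contrast it describes but does not transfer to the primary tests named in the Analysis section. On the inputs of that claim, the loss is from about .81–.83 to about .67 for a joint test. Across the other readings tried, the joint test ranges from .41 to .95, so .67 is the consequence of the stated planning inputs and not an expected power for the trial.

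The shape restriction is certain: no quadratic through zero holds 6 lb at four visits. Its effect on the maintenance aim is conditional. With early onset and compound symmetry, a constant benefit is fitted as falling from 6.3 to 4.8 lb between months 9 and 12.

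**What to change.** Keep baseline in the response vector with equal baseline means. Fit time as categorical with group-by-visit effects, and name the baseline-versus-mean-follow-up group contrast as the single primary test. Report the 6-month and 12-month differences as separate named contrasts for the loss and maintenance aims, and keep the polynomial as description.

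Do not substitute the 6-month difference alone or the 4-df omnibus test: on the same inputs they have about .62 and .63, less than the test being replaced.

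The cost is wording and a few more mean parameters, with no added participants, visits or data. There is a small downside. The averaged contrast does not itself separate 6-month loss from 12-month maintenance, and it loses power if the effect builds slowly (about .72 for 0,3,6,6,6, the same as the 2-df test).
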